### Blinding

The patient, the local clinical team assessing the patient during the follow-up period and the research team assessing endpoints will all be blinded to which arm the patient was assigned to.

### Study endpoints

The primary study endpoint is an episode of sustained atrial arrhythmia (Fig. 3) occurring at any time in the 12-month period after catheter ablation. There will be a 2-month blanking period after ablation in which atrial arrhythmias are not considered. Endpoints are assessed at 3, 6, 9 and 12 months. An atrial arrhythmia (atrial fibrillation, atrial flutter, atrial tachycardia) is defined (> 30 s) on a Holter Monitor or documented on a single 12 lead ECG [9]. As patients with AT recurrence may degenerate to Afib at the time of ECG, it was included as a primary endpoint. The date of recurrence for each atrial arrhythmia will be recorded. In addition to any ECG and Holter Monitors performed by the clinical team, all patients will undergo an additional 24-h Holter at 12 months.

**Fig. 3 Fig3:**
[figure not shown]
Ripple AT Plus study workflow

### Secondary endpoints

Other secondary endpoints measured are:Acute procedural success (defined by restoration of sinus rhythm through ablation without need for DCCV)Procedure timeAblation delivered (lesion number and length of ablation set)

### Endpoint adjudication

Primary endpoints will be assessed at 3-, 6-, 9- and 12-month intervals by a blinded researcher. They will review all clinical data (including Holter’s and ECG’s) for evidence of atrial arrhythmia, as well as recording the results of a further 24-h Holter at 12 months. Endpoint adjudication will be done by an independent Adjudication Committee (EAC). The EAC will centrally review all recurrences to ensure they have been classified correctly.

### Sample size calculation

The sample size for this study is based on previous evidence published by our group. In a non-randomised, prospective study comparing ripple mapping–guided ablation to conventional mapping–guided ablation, the diagnostic accuracy was 90% and 65% respectively [10]. A similar effect size was also seen in a randomised prospective study (Ripple-AT Study), showing acute success was 90.5% and 70.7% respectively. In order to detect a difference between arms with 90% power and an alpha value of 0.05, at least 80 patients would be needed to be randomised to each treatment arm. Accounting for potential non-completion of protocol (10%) and loss to follow-up (10%), a minimum of 200 patients will need to be enrolled. Power calculations were performed using the G*Power software (University of Dusseldorf).

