## Methods

### Study design

Ripple-AT Plus (ClinicalTrials.gov identifier number NCT03915691) is planned as a prospective, multicentre, single-blinded, randomised controlled superiority trial. The protocol was approved by the research ethics committee 19/LO/0637.

The target recruitment number is 200 with a 1:1 randomisation to either a “Ripple Map scar thresholding”-guided isthmus ablation or a “conventional mapping and ablation”. The primary end-point is documented ECG or Holter recurrence of any atrial arrhythmia which will be assessed at 3, 6, 9 and 12 months. All patients will undergo a 24-h Holter at 12 months.

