This trial follows on from the Ripple AT study from our group, which was the largest ever randomised mapping trial involving scar-related atrial tachycardia [7]. This study demonstrated that ripple mapping scar thresholding was superior to Local Activation Time mapping in guiding successful ablation. In a sub-analysis of the peri-mitral circuits later published from this study [14], almost 4/5 cases had a clear isthmus bounded by scar, < 1 cm in length and identifiable using Ripple Mapping with a 100% termination rate when targeted for ablation. In contrast, conduction block was difficult to achieve using linear ablation of the conventional posterior mitral isthmus and often required long anatomical ablation lines with more than double the amount of ablation. In this study, crossover between mapping arms was permitted; therefore, it remains unknown whether using the ripple mapping scar thresholding technique to guide ablation translates to longer term arrhythmia freedom. Follow-up data from this study (unpublished) showed a 25% recurrence, all atrial arrhythmia over 12-month follow-up showing a clear need to prioritise longer-term outcomes, instead of acute ablation success [7].

We feel the ripple mapping scar thresholding technique is the gold standard for diagnosing the “narrowest isthmus” and is robust enough to standardise in a multi-centre approach. As this software is commercially available, it can be applied worldwide.

This study may offer insight into the patient characteristics that may not respond well to ablation. Whether a certain burden of scar portends early recurrence is important in clinical selection of individuals that are referred for ablation, particularly with the acceleration of conduction system pacing and AV node ablation as an alternate treatment strategy [15, 16].

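### The stated 90% power belongs to acute success, a secondary endpoint, and is not shown for 12-month recurrence, the primary endpoint

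*Protocol article*

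**What the plan says.** All references are to the protocol article.

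- **Study endpoints:** the main outcome is defined thus: "The primary study endpoint is an episode of sustained atrial arrhythmia (Fig. 3) occurring at any time in the 12-month period after catheter ablation", with a 2-month blanking period.
- **Secondary endpoints:** acute procedural success, meaning sinus rhythm restored by ablation without cardioversion, is listed here. Diagnostic accuracy is not among the listed endpoints.
- **Sample size calculation:** two earlier results are cited. One is a non-randomised study with diagnostic accuracy of 90% vs 65%. The other is the randomised predecessor trial, "showing acute success was 90.5% and 70.7% respectively". The section then states: "In order to detect a difference between arms with 90% power and an alpha value of 0.05, at least 80 patients" per arm, raised to 200 for 10% non-completion and 10% loss to follow-up. No recurrence rate or recurrence difference appears.
- **Discussion:** unpublished follow-up of the predecessor trial "showed a 25% recurrence, all atrial arrhythmia over 12-month follow-up". The same paragraph notes that crossover between mapping arms was allowed, says it is not known whether ripple guidance carries over to longer-term freedom from arrhythmia, and argues that long-term outcome should take priority over acute success.

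**The concern.** A power statement in a superiority trial is read as applying to the primary endpoint. Here the inputs describe what happens in the laboratory on the day, whereas the primary endpoint is what happens to the patient up to month 12. The step from one to the other is what the trial sets out to test, and the Discussion calls it unknown. The one long-term figure in the document is not used.

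Readers will take 90% as the chance of detecting a worthwhile effect on recurrence. If the primary result is not significant, that figure would lend it more weight as evidence of no benefit than the design has been shown to support.

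**Working it through.** **Inputs.** Acute success 90.5% vs 70.7%, diagnostic accuracy 90% vs 65%, alpha 0.05, power 90%, 80 per arm and the attrition allowances come from Sample size calculation. The 1:1 allocation comes from Study design. The 25% recurrence comes from the Discussion. Sidedness is not stated; two-sided is assumed.

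**Formulas** (comparison of two proportions, pooled variance under the null, p̄ the mean of p1 and p2):

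n per arm = [1.960·√(2p̄(1−p̄)) + 1.282·√(p1(1−p1)+p2(1−p2))]² / (p1−p2)²

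power = Φ{ [|p1−p2|·√n − 1.960·√(2p̄(1−p̄))] / √(p1(1−p1)+p2(1−p2)) }

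**Step 1: reproduce the 80.**

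- Acute success: p̄ = 0.806. n = (1.960×0.5592 + 1.282×0.5414)² / 0.198² = (1.0961 + 0.6938)² / 0.0392 = 81.7, so 82. Unpooled and arcsine versions give 79. Power at 80 per arm = Φ[(1.7710 − 1.0961)/0.5414] = Φ(1.247) = 89%. The 80 is reproduced.
- Diagnostic accuracy: the same formula gives 57 per arm (65 with continuity correction), and 97% power at 80. The 80 is not reproduced.
- Other versions for acute success fit less well: 92 (two-sided, continuity-corrected), 67 (one-sided), 77 (one-sided, continuity-corrected).
- Attrition: 160/(1 − 0.20) = 200. Consistent.

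**Step 2: apply the same design to recurrence.** The document gives no rate per arm, so every pair below is an assumption. The 25% can be read as the control rate or as the average of both arms, and the two readings must be kept apart.

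Worked example, 25% vs 12.5%: p̄ = 0.1875; power at 80 = Φ[(0.125×√80 − 1.960×0.5520)/0.5449] = Φ[(1.1180 − 1.0819)/0.5449] = Φ(0.066) = 53%.

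| Reading of the 25% | Conventional vs ripple | Power at 80 per arm | n per arm for 90% |
|---|---|---|---|
| Control rate | 25% vs 15% | 35% | 335 |
| Control rate | 25% vs 12.5% | 53% | 203 |
| Control rate | 25% vs 10% | 71% | 133 |
| Control rate | 25% vs about 6.6% | 90% | about 80 |
| Two-arm average | 30% vs 20% | 31% | 392 |
| Two-arm average | 33.3% vs 16.7% | 69% | 140 |
| Two-arm average | 35% vs 15% | 84% | 97 |
| Two-arm average | about 36% vs 14% | 90% | about 80 |
| Neither (higher control rate) | 40% vs 17% | 90% | about 80 |

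Halving recurrence is 25% vs 12.5% on the first reading (overall rate 18.75%) and 33.3% vs 16.7% on the second (overall rate 25%). That is why its power is 53% in one case and 69% in the other.

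**Step 3: suppose the acute effect carried over in full.** The ratio of acute failures is 9.5/29.3 = 0.32. Applied to a 25% control rate it gives 25% vs 8.1%, power 83%; with 25% as the average it gives 37.8% vs 12.2%, power 97%. Carrying over the 19.8-point difference instead gives 25% vs 5.2%, power 95%, or 34.9% vs 15.1%, power 83%.

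**Step 4: no attrition (100 per arm).** Power is 62% for 25% vs 12.5% and 91% for 35% vs 15%.

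**The case against.** The strongest reply is that the power for recurrence cannot be called too low, because the document commits to no recurrence rate in either arm. This stands. A reader might infer that the trial lacks 90% power for its primary endpoint; the document does not support that. With 40% vs 17% the power is 90%, with 37.8% vs 12.2% it is 97%, and full carry-over of the acute effect gives 83% to 97%.

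A reader might also infer that a large benefit would probably be missed. That goes too far as well: halving has 53% or 69% power, and 35% vs 15% has 84%.

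The 25% is itself a weak anchor. It is unpublished and not split by arm, and it comes from a trial with crossover. This also stands, and is why a range is shown. It is a reason to state an assumption openly, but it does not justify having none.

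It could be said that an article condenses the full protocol. That does not help here. The section sets out its basis, alpha, power, attrition and software, and the outcomes it names are not the primary endpoint.

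**Conclusion.** The point holds in this form: the 90% power with 80 per arm is a calculation for acute success, a secondary endpoint, and no power is shown for 12-month recurrence. Diagnostic accuracy is cited in support but does not produce the 80.

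On the document's only recurrence figure, power falls below 90% unless the effect is very large: a drop from 25% to about 6.6% (18 points), or about 36% vs 14% (22 points). For 10-point reductions it is 31% to 35%.

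These figures assume a two-sided 0.05 test of two proportions with 80 evaluable patients per arm. The recurrence rates per arm are assumptions throughout.

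**What to change.** Keep the enrolment target at 200 and amend the sample size section in three places.

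1. Label the 90.5% vs 70.7% calculation as power for the secondary endpoint, acute success.
2. State the 12-month recurrence rate assumed in each arm, with the reason for it, and note the limits of the 25% figure.
3. Replace the general 90% statement with power, or the detectable difference, for 12-month recurrence over a range of control rates. Present the control-rate and overall-rate scenarios separately, so that no sentence combines a 25% overall rate with a 25% control rate. State whether alpha is two-sided.

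The cost is a rewording and a less favourable stated power. No extra patients are required. The Progress section reports 33 patients randomised, so the statement can be corrected well before results.

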### Progress

This study currently has 3 recruiting NHS sites with an aim of at least 10 UK centres. It commenced recruiting in October 2022 and has randomised 33 patients to date.

## Discussion

The Ripple-AT Plus Study is the first blinded randomised trial that considers long-term outcomes in s-AT ablation. It will compare ablation targeting the “narrowest isthmus” identified using the ripple mapping scar thresholding technique [11], against conventional mapping (e.g. LAT mapping) and ablation techniques, which often employs standardised anatomically defined linear lesions. At present, it is not known whether targeting a narrower isthmus leads to improved outcomes.

There has been significant progress over the last decade in high-density 3D mapping techniques. Despite this, in real-world practice, operators continue to deliver standardised anatomical lesions, which can require more extensive ablation delivery. High-density mapping allows us to appreciate narrower isthmuses, which may require less ablation [11, 12]. Curtailing the amount of ablation delivery will reduce the amount of iatrogenic scar created, with scar known to act as a nidus for future arrhythmia recurrence [13]. As ablation invariably creates new scar, we hypothesise less ablation is less pro-arrhythmic, and this will be studied in a randomised fashion. However, whether a narrow isthmus mapped in tachycardia is truly narrow (bordered by fibrosis) or bordered by refractory tissue observed at a faster atrial cycle length (i.e. functional block) is unknown. This will be analysed with remapping in sinus rhythm post ablation.

This trial follows on from the Ripple AT study from our group, which was the largest ever randomised mapping trial involving scar-related atrial tachycardia [7]. This study demonstrated that ripple mapping scar thresholding was superior to Local Activation Time mapping in guiding successful ablation. In a sub-analysis of the peri-mitral circuits later published from this study [14], almost 4/5 cases had a clear isthmus bounded by scar, < 1 cm in length and identifiable using Ripple Mapping with a 100% termination rate when targeted for ablation. In contrast, conduction block was difficult to achieve using linear ablation of the conventional posterior mitral isthmus and often required long anatomical ablation lines with more than double the amount of ablation. In this study, crossover between mapping arms was permitted; therefore, it remains unknown whether using the ripple mapping scar thresholding technique to guide ablation translates to longer term arrhythmia freedom. Follow-up data from this study (unpublished) showed a 25% recurrence, all atrial arrhythmia over 12-month follow-up showing a clear need to prioritise longer-term outcomes, instead of acute ablation success [7].

We feel the ripple mapping scar thresholding technique is the gold standard for diagnosing the “narrowest isthmus” and is robust enough to standardise in a multi-centre approach. As this software is commercially available, it can be applied worldwide.

This study may offer insight into the patient characteristics that may not respond well to ablation. Whether a certain burden of scar portends early recurrence is important in clinical selection of individuals that are referred for ablation, particularly with the acceleration of conduction system pacing and AV node ablation as an alternate treatment strategy [15, 16].

The COVID-19 pandemic enforced long-term changes in healthcare towards remote working, implementing digital systems that support the safe online sharing of clinical information. CARTONET is a secure, simple to use and efficient cloud-based AI/machine learning system that offers access to clinically relevant data-sets from the CARTO system remotely from the hospital premises. We have already demonstrated the feasibility of this technology as a research tool in analysing the first cases recruited to the Ripple AT PLUS study from different hospitals (Fig. 4) [17]. Our study will examine its ability to improve the efficiency of multicentre clinical electrophysiology research on a larger scale.

**Fig. 4 Fig4:**
[figure not shown]
Graphical dataset presented using CARTONET™. Summarised graphical dataset for the first 8 study cases presented by CARTONET™ (including total procedural duration, mapping vs ablation times, ablation lesions)

## Limitations

This study uses standard binary clinical endpoints with ECG or Holter evidence to define recurrence as opposed to continuous monitoring.

Operator experience may bias diagnostic ability within each interventional arm, though a multicentre approach with numerous operators may mitigate against this.

This study does not seek to influence anti-arrhythmic drug usage, and it is possible that this may differ between arms.

The conventional arm the protocol is permissive allowing numerous different approaches which may make the comparator arm heterogeneous.

## Summary

This study hopes to determine whether targeting the narrowest isthmus identified using the ripple mapping scar thresholding technique in s-AT ablation leads to longer-term freedom from arrhythmia when compared to a conventional approach.
